**Fig. 3 Fig3:**
[figure not shown]
Power and sample size estimates based on small, medium, and large intervention effect sizes and covariates

### Recruitment {15}

Participants are recruited internally within the community-based FQHC. The clinic data team regularly creates, updates, and shares a list of potentially eligible patients based on their recent HIV care history with the research team. Clinic staff also help to recruit from their patient population by reviewing clinic schedules weekly to identify participants with a pending appointment who might qualify based on the eligibility criteria for on-site recruitment. Other clinic staff, such as case managers and general medical staff, are informed of study details and eligibility to provide preliminary study information and refer potential participants. Research staff also work with other teams within the HIV Department to promote the study. The clinic’s community advisory board also serves as a resource for informing potential participants that the study is occurring, and study participants can also refer friends. When a patient is identified to be potentially eligible for the study (e.g., through clinic staff referral, or by reviewing clinic data), study staff attempt to recruit the individual, usually by phone. Study staff introduce the study and provide the next steps for interested patients. Those not interested are given an opt-out option to limit further contact from the team.

## Assignment of interventions: allocation

### Sequence generation {16a}

Enrolled participants are randomized on a 1:1 basis into the PATH intervention or usual care. Randomization is determined using an online generated randomization schedule determined prior to the study launch (a priori). Randomization is not stratified by substance use or race, although recruitment efforts are made to help ensure that at least a third of the sample are people with active substance use (defined as using non-prescription stimulants or opioids in the past 6 months) and that the sample is representative of the HIV patient population at the community-based FQHC (i.e., at least 60% Hispanic).

### Concealment mechanism {16b}

Once a participant completes enrolment procedures, a research staff member (peer navigators are not research staff) completes an online enrollment verification and randomization form (via Qualtrics). The form was pre-programmed by the PI and Study Coordinator in such a way that the study arm is revealed to the staff member once the participant ID is assigned and entered. Participant ID number determines study arm assignment (as defined by the online generated randomization schedule). This method ensures that both the study arm and sequence of assignments are concealed until conditions are assigned.

### Implementation {16c}

The allocation sequence was determined randomly using an online generated randomization scheduling tool, and study staff are trained to enroll participants in their preferred language (English or Spanish).

## Assignment of interventions: blinding

### Who will be blinded {17a}

Enrolled participants are not blind to their study assignment (they know if they are assigned a peer navigator and have access to the PATH web app or not), and neither are peer navigators nor HIV care providers. Staff who complete chart abstraction for outcome assessment and data analysts are blinded to study arm assignment.

### Procedure for unblinding if needed {17b}

The design is an open label with only outcome assessors and data analysts being blinded so unblinding will not occur.

## Data collection and management

### Plans for assessment and collection of outcomes {18a}

To measure the primary outcome, sustained viral suppression, viral load data will be collected through medical chart review (within a 30-day window of when the 6- and 12-month follow-ups are due). Participants who do not have a viral load in the chart within the 30-day (pre/post) window are invited to go to any Quest lab location for a blood draw to collect viral load information for study purposes. For participants randomized into the PATH intervention arm, peer navigators offer reminders of when labs are due as part of usual HIV care. For participants randomized into the control arm, if a study-related lab is overdue, then they are notified by research staff at the community-based FQHC and encouraged to complete a blood draw at a Quest lab. Secondary outcomes, retention in HIV care and gaps in HIV medical visits, will be assessed through medical chart review. Self-reported ART adherence will be measured using the Wilson-3 scale [28], a continuous measure of ART adherence (0–100; 100 = perfect adherence).

Other trial data measured at baseline and follow-up include sociodemographic information (e.g., age, gender, race, sexual orientation, years living with HIV), as well as validated measures on ART adherence-related information, motivation, and behavioral skills [42, 47], eHealth literacy [48], technology use [49], rapport with an assigned peer navigator, HIV-related stigma [50], social support [51], medical mistrust [52], depressive symptoms [53], PTSD [54], experiences with violence [55, 56], food security [57], housing instability [58], substance use [59], substance use-related stigma [60], and substance use treatment history.

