### Outcomes {12}

The primary outcome in this trial is sustained viral suppression, defined as an HIV viral load at 6 and 12 months post-enrollment of less than 200 copies/mL. Secondary outcomes include the following variables: *Retention in HIV care* (at 6- and 12-month follow-up) is assessed through chart review using the HRSA definition of having greater than or equal to 2 HIV medical visits at least 90 days apart within the 12-month follow-up. *Gap in HIV medical visits* is measured through chart review at 6 and 12 months using the HRSA definition (no HIV medical visits in the last 6 months) [43]. *ART adherence* is measured using the self-report Wilson-3 scale [28] at 3-, 6-, 9-, and 12-month follow-up. The secondary outcomes were chosen to fill gaps in outcome measurements in the HIV peer navigation intervention literature [17] and to have a broader representation of the stages of engagement in the HIV care continuum [4].

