The primary analytic approach will utilize generalized mixed-effects models and an intent-to-treat (ITT) approach. This addresses issues with attrition, missing data, and other unintended violations of design, thereby allowing us to maximize statistical power by not excluding subjects with some missing data. Mixed-effects models incorporate random intercepts and slopes for each participant based on the participant’s multiple measurements over time [65]. Intra-class correlations among participants nested within specific peer navigators will be examined to diagnose whether significant variation in outcomes is explained by the shared peer navigator, if so, models will account for clustering. Attrition analyses will compare participants who complete all measurements to those who do not based on baseline characteristics. If there is a baseline imbalance between participants retained in the study versus not across certain characteristics, then these will be accounted for in all analyses. In addition, maximum likelihood will be used to address incomplete data because this makes the relatively mild assumption that missing data are conditionally missing-at-random [66]. Outcome analysis will apply a priori planned comparisons. It is hypothesized that compared to control, participants in the PATH intervention will exhibit the following: greater viral suppression at 6- and 12-month follow-up (HYP 1); greater retention in care (HYP 2); fewer gaps in HIV care (HYP 3); greater ART adherence (HYP 4). HYP 1–3 involve binary outcomes (Y/N on sustained viral suppression, retained in care, had gaps in care), while HYP 4 is a continuous outcome (proportion). These hypotheses will be tested using regression analysis specifying the appropriate outcome distribution (e.g., binomial) and function (e.g., logit), with *α* = .05; any subsequent post-hoc comparisons will be adjusted via simulation-based stepdown methods [67] to maintain a nominal type 1 error rate of .05. For the primary outcome sustained viral suppression, we will assume non-suppression at that time point (6 or 12 months) for any missing viral load chart data. A sensitivity analysis will be conducted utilizing only available viral load chart data to compare with the results assuming missing viral load equals non-suppression.

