## Oversight and monitoring

### Composition of the coordinating center and trial steering committee {5d}

The trial is being implemented with the support of trained research staff, including a project manager who is responsible for monitoring study activities for the purpose of creating weekly recruitment and enrolment reports and a study coordinator who is based on-site at the community-based FQHC and is responsible for overseeing recruitment, enrolment, and follow-up survey collection. The study coordinator receives supervision and guidance from the Principal Investigators (including the Site Principal Investigator), a research supervisor at the community-based FQHC, and the HIV Clinical Services Manager at the community-based FQHC. Other staff include trained individuals who are bilingual and receive training in recruitment and/or enrolment. Peer navigators are not considered research staff and are not involved in recruitment, enrollment, and follow-up procedures with participants. Altogether, the investigative team is responsible for providing scientific guidance and oversight around the design and implementation of the trial. Data are being managed collectively by the project manager, study coordinator, Principal Investigator, and Site Principal Investigator.

The development and implementation of the study also received advisement from two pre-existing community advisory boards, one at the community-based FQHC (comprised mainly of patients living with HIV who have stayed retained in care and have maintained viral suppression) and the other is a board that provides advisement to HIV-related research studies focused on addressing health equity. The two boards provided input on the design of the trial and the PATH intervention, are given updates about the trial, and provide ongoing input on an annual basis.

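### Outcome labs are prompted differently in the two arms while a missing viral load counts as non-suppression, so unequal lab attendance can create or hide a PATH effect

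*Protocol article*

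**What the plan says.** All places are in the protocol article.

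- **Outcome.** Outcomes {12} makes sustained viral suppression primary, "defined as an HIV viral load at 6 and 12 months post-enrollment of less than 200 copies/mL". Both time points must be suppressed.
- **Source and window.** Plans for assessment and collection of outcomes {18a} takes viral loads from the chart "within a 30-day window of when the 6- and 12-month follow-ups are due". Participants of either arm without such a value "are invited to go to any Quest lab location for a blood draw to collect viral load information for study purposes".
- **Prompt in PATH.** Same section: "For participants randomized into the PATH intervention arm, peer navigators offer reminders of when labs are due as part of usual HIV care".
- **Prompt in control.** Same section: "if a study-related lab is overdue, then they are notified by research staff at the community-based FQHC", and they are encouraged to have blood drawn at Quest.
- **Missing values.** Statistical methods for primary and secondary outcomes {20a}: "we will assume non-suppression at that time point (6 or 12 months) for any missing viral load chart data".
- **Check on that rule.** Same section: "A sensitivity analysis will be conducted utilizing only available viral load chart data to compare with the results assuming missing viral load equals non-suppression".

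**The concern.** Three things differ between the arms in how an outcome lab is prompted: who does it (peer navigator or research staff), when (due or overdue), and whether the prompt is part of the tested intervention. Under the missing-value rule, a participant counts as a success only if suppressed at both times and measured at both times. Whether a measurement exists is thus a component of the primary outcome, and the article sets up different routes to it in each arm.

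If the routes perform equally well, nothing is lost. If they do not, the primary comparison mixes an effect on suppression with an effect on having blood drawn, and hypothesis 1 concerns only the former. The planned sensitivity analysis helps in some circumstances but not in the most plausible ones.

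**Working it through.** **Inputs from the article.** Up to 375 randomised 1:1, up to 20% attrition, about 300 analysed (Sample size {14}); alpha 0.05; planning odds ratio 1.57; a retention goal of at least 80% at each study visit (Discussion).

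**Assumed, because the article does not give them.** True sustained suppression p, equal in both arms: 65%, with a range of 50% to 80%. Availability a, the probability that both viral loads are present: scenarios below. A two-sided test, since sidedness is not stated.

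**Step 1: the plan's own figure.** 375 × (1 − 0.20) = 300, or 150 per arm, which agrees. Scoring missing as failure keeps everyone randomised in the primary analysis, so the relevant number here is 375 / 2, about 187 per arm.

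**Step 2: observed success rate.** If missingness is unrelated to suppression, observed rate = p × a. With p = 0.65 and no true effect:

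| Availability PATH v control | Observed PATH | Observed control | Difference | Odds ratio |
|---|---|---|---|---|
| 80% v 80% | 0.520 | 0.520 | 0 | 1.00 |
| 85% v 80% | 0.5525 | 0.520 | +3.3 points | 1.14 |
| 90% v 80% | 0.585 | 0.520 | +6.5 points | 1.30 |
| 80% v 85% | 0.520 | 0.5525 | −3.3 points | 0.88 |
| 80% v 90% | 0.520 | 0.585 | −6.5 points | 0.77 |

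**Step 3: chance of a significant result.** Pooled two-proportion z test: P(significant for PATH) = Φ((d − 1.96 × SE0) / SE1). Here d is the difference, SE0 = √(2 × p̄(1 − p̄) / n) with p̄ the mean of the two observed rates, and SE1 is the unpooled standard error.

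- 80% v 80%: 2.5%, the nominal value.
- 85% v 80%: d = 0.0325, SE0 = 0.0516, SE1 = 0.0515, so Φ(−1.33) = 9%.
- 90% v 80%: d = 0.065, SE0 = 0.0514, SE1 = 0.0513, so Φ(−0.70) = 24%.
- With the gap reversed, the same probabilities apply to a significant result against PATH.

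Over p = 50% to 80%, 85% v 80% gives 2.5 to 4.0 points and 7% to 13%; 90% v 80% gives 5 to 8 points and 16% to 38%.

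**Step 4: what the available-data analysis does.** If missingness is unrelated to suppression within each arm, it compares 65% with 65% and removes the bias. If missingness depends on suppression, it need not. Assume p = 0.65 in both arms, with labs obtained from 95% of suppressed and 81% of unsuppressed PATH participants, and from 90% and 61% in control.

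- Overall availability: 0.65 × 0.95 + 0.35 × 0.81 = 0.901 in PATH; 0.65 × 0.90 + 0.35 × 0.61 = 0.799 in control.
- Primary rule: 0.65 × 0.95 = 0.6175 v 0.65 × 0.90 = 0.585, which is +3.3 points for PATH.
- Available data: 0.6175 / 0.901 = 68.5% v 0.585 / 0.7985 = 73.3%, which is −4.7 points.

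Neither analysis returns the true difference of zero, and they err in opposite directions.

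**Step 5: is there room for such gaps?** If viral loads went missing at the rate tolerated for study visits, and misses at the two times were independent, 1 − 0.80² = 36% would lack at least one. This is orientation only: the retention goal covers study visits, and chart viral loads can exist for someone who misses a survey.

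**The case against.** **Direction.** A reader might infer that the design biases the result towards PATH. The article does not support that. It states who prompts and when, but not the yield. Peer reminders are described as part of usual HIV care, while controls with an overdue lab are actively contacted and steered to Quest; that could capture as many labs or more. This objection stands.

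**Access to a lab.** The Quest invitation is worded for anyone without an in-window value, so the arms do not differ in access, and this should narrow any gap. Quest results are already outcome data: the biological specimens section {33} says they are abstracted. What remains unequal is the prompt.

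**The sensitivity analysis.** It would be wrong to say that the planned analyses cannot separate suppression from attendance. Under the assumption in Steps 2 and 3, the available-data analysis does so fully. It stops doing so when missingness is tied to suppression, as in Step 4. That is hard to rule out in a population that the Discussion calls poorly engaged in care or at risk of falling out of it.

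**Role of the peers.** One might read a contradiction into the oversight section {5d}, which says "Peer navigators are not considered research staff and are not involved in recruitment, enrollment, and follow-up procedures with participants". Reminders given as part of usual care can be read as outside study follow-up, so the passages do not clearly conflict.

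**Other safeguards.** Blinding of chart abstractors and analysts {17a} does not affect whether a test was done. Maximum likelihood has no missing primary-outcome values to work on once they are set to failure. Section {20c} names inverse probability weighting and multiple imputation as general options but does not tie either to the primary outcome.

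**Conclusion.** The concern holds as a risk of ascertainment bias in the primary contrast, of unknown direction and size. It rests on two stated features: arm-specific lab prompts, and missing scored as failure at either of two required times. The figures in Steps 2 and 3 are scenarios that depend on the assumed suppression rate and on missingness unrelated to status. They show that an attendance gap of 5 to 10 points is enough to raise the one-directional error rate from 2.5% to 9% or 24% at 65% suppression. They do not show that such a gap exists. The planned available-data analysis is a partial safeguard, valid only if missingness is unrelated to suppression within each arm.

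**What to change.** 1. For all remaining follow-up, have the same research staff issue study-lab prompts and Quest invitations to both arms on one identical schedule. Peers may continue their own contacts as part of the intervention.
2. Keep missing = non-suppression as the primary rule. Making imputation primary would be a trade-off that the problem does not require.
3. Add a sensitivity analysis of the primary outcome that does not assume missingness unrelated to suppression: either multiple imputation by arm, using baseline and out-of-window viral loads, visit attendance and reported adherence, or a tipping-point analysis varying the suppression rate among those missing, separately by arm.
4. Report viral-load availability at 6 months, 12 months and both, by arm, beside the primary result.

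The cost is a few more reminder contacts and some programming. Recruitment began in November 2021, so labs already prompted under the existing procedure can be addressed only through items 3 and 4.

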### Plans to promote participant retention and complete follow-up {18b}

A study coordinator who is based on-site at the community-based FQHC is responsible for overseeing study retention/follow-up survey collection. Strategies to promote study retention include the use of a comprehensive “locator form” completed during the enrolment process, whereby each participant is asked about various and preferred methods (e.g., phone, email, text) they may be contacted to allow for staff to send follow-up survey reminders. Staff are trained to update the locator form during contact with the participant at each follow-up assessment. The study coordinator attempts to contact participants up to 2 weeks before the next follow-up survey is due and continues to attempt contact through various methods until 45 days after the follow-up is due (after which point the visit is considered missing). In addition, the study coordinator visits clinic locations on a regular basis to provide on-site support to participants who may prefer to complete their survey on-site at the community-based FQHC (accessing the survey on Qualtrics through an office computer or tablet).

### Data management {19}

All data for this trial are collected via an online survey platform, Qualtrics (Provo, UT; First released in 2005; version used was current at the time of study activities). Baseline and follow-up surveys are self-administered by participants, although study staff are available at all times to answer any questions that might arise during survey completion. Case report forms, including medical chart abstraction data, are entered by trained study staff. Qualtrics complies with applicable data privacy laws in its role as a data controller of its own data and as a data processor of customer data. All data are backed up by Qualtrics using two methods: automatic propagation across servers (immediate upon collection) and daily complete off-site encrypted backups. In addition, the study’s project manager conducts monthly back-ups of all data. Data managers are responsible for examining frequencies for categorical variables (e.g., education) and measures of central tendency for continuous variables (e.g., age). Range checks were defined, a priori, for every variable, and out-of-range values are automatically flagged and reported in reports compiled semi-annually. This process assists with the detection of missing data prior to outcome analysis.

### Confidentiality {27}

This trial takes precautions to protect participants’ confidential information (for example, HIV status and drug use). Participants are only identified in the study by a participant ID number. All data collected from recruited and enrolled participants, including electronic data, are identified only by the participant’s study ID and are protected against access by anyone except authorized staff connected to the study. Any hard copy data are stored in locked cabinets in secure offices, while electronic data are password-protected. HIV status or illicit drug use information does not appear along with any personal identifying information such as the locator form. The locator form containing participants’ contact information is completed online over Qualtrics. The computer file that contains the key to participants’ code numbers (name-to-ID relational file) is encrypted, and the computers on which the file resides are locked in the study coordinator’s office. Only authorized PATH trial staff are able to remove encryption from the computer file. Other security mechanisms include security workshops and written security policies and procedures. For example, all study staff are required to receive certification in “Information, Privacy, and Security” training, offered via the Collaborative Institutional Training Initiative (CITI) program. Protections against breaches of confidentiality are also implemented on the PATH webapp. Specifically, user profiles are monitored by study staff and protected from personal identifying information, to maintain the participant’s confidentiality, and all other features of the webapp are monitored in the same way. Finally, participant responses on surveys remain confidential and are not shared with their medical care providers or staff at the community-based FQHC. Once all data have been collected for the trial, the datasets will de-identified prior to analysis.

### Plans for collection, laboratory evaluation, and storage of biological specimens for genetic or molecular analysis in this trial/future use {33}

Biological specimens for HIV viral load are not being directly collected by the researchers of this trial. Instead, HIV viral load data will be abstracted from medical record (chart) information already being collected as part of UC at the community-based FQHC, or through abstraction of Quest lab results (as described in Item 18). Relatedly, the trial is not conducting any laboratory evaluation or storage of any other biological specimens.

